#### Aim 2: Delphi process for questionnaire reduction

We will use a modified Delphi approach drawing on a panel of South African experts relevant to health system strengthening and organisational change to assess the content validity of the TCU-ORC items and identify areas for potential adaptation, cultural modification and item reduction. The Delphi method is well suited to measure adaptation^34^ and over the past decade has been used widely to gain expert consensus in health research.^35–37^

We will use snowball sampling to identify up to 30 experts to participate in the Delphi process. Experts will be identified within three panels—Panel 1 Academics and researchers; Panel 2 Governmental service providers and Panel 3 Non-governmental service providers. We will approach academics from a variety of institutions and across different provinces of South Africa. Service providers approached will be from the national level, as well as provincial and district level within the Western Cape province. The expert panels will therefore be broadly representative of the various regions in the country and will consist of individuals with experience in health systems research and development, as well as health service delivery.

The Delphi approach will involve electronic surveys to assess experts’ opinions on the suitability of TCU-ORC items, providing anonymised reports on the aggregated opinion data to participants, and allowing participants to reassess (and modify) their judgements after receiving feedback on the group opinions in order to guide a consensus-building process on the content validity of the measure.^38 39^ The methods enable assessment of consensus between the panels, and points of divergence according to roles. During the surveys, experts will be asked to rate each item on the ORC according to its (1) relevance to chronic disease management in South Africa, (2) relevance to adoption of evidence-based practice, (3) relevance given health system resource constraints and (4) evaluability in South African PHC context. Two rounds of anonymous rating of the items and feedback on responses will be conducted. Any items achieving less than 70% consensus will be excluded.^40^ This stage will be followed by a face-to-face expert meeting incorporating nominal group methods to discuss findings from phases I and II of the study and how these can be combined to shorten the TCU-ORC assessment. The combination of these methods has previously been shown to be useful for adapting a multidomain, multi-item, US-developed primary care assessment tool for the South African context.^40^

### Analyses

Analyses will follow the processes of similar validation studies.^15 41 42^ STATA statistical software will be used for analysis and modelling. Multiple logistic regression analysis will be used to examine the association of demographic characteristics with TCU-ORC scores. Internal consistency of the TCU-ORC and subscales will be assessed by calculating Cronbach’s alpha coefficients. For the retest sample, we will calculate the intraclass correlation coefficient to determine the test-retest reliability of the various scales. To assess the convergent validity of the ORC, correlation coefficients will be used to give evidence for correlation between the ORC, ORCA and CARI measures. To evaluate the construct validity of the TCU-ORC, we will examine the factor structure with both exploratory and confirmatory factor analysis. First, principal component analysis^43^ with oblimin rotation will be used to examine the generalisablity of the factor structure of the original questionnaire to the South African data. Principal axis factoring will then be conducted to give further evidence of the factor structure.^43^ Confirmatory factor analysis will be used to confirm whether the latent structure of the TCU-ORC identified in HIC is a good fit for the South African data.^43^ Structural equation modelling techniques will be employed and acceptability of model fit data reported.

Based on the findings from these analyses, and to fulfil the secondary aim of the study, a shortened version of the TCU-ORC scale will be developed. Loading of items onto factors will be assessed to guide decisions around the relevance of each item and whether to retain each in the shortened tool. Data analysis from the administration of the instruments and from the Delphi process will be integrated into an approach for shortening the existing TCU-ORC scale.

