Despite the drive to integrate MNS services into chronic disease care in LMICs, there has been little investigation of ORC in these settings. Questions about how to assess ORC accurately have hampered the study of organisational readiness for MNS services in LMIC health systems. There are a variety of well-developed scales for assessing ORC and other implementation factors in HIC contexts.^23^ The Texas Christian University ORC (TCU-ORC) scale^24^ is among the most widely used of the ORC scales, and has been tailored for use in health service research.^20^ A recent systematic review covering ORC measures specifically highlighted that only 7 of the 43 measures reviewed had evidence for their validity and reliability.^25^ It identified the TCU-ORC scale as having the strongest evidence for validity of all measures assessed. Studies in HIC contexts have shown that this measure has adequate internal consistency and good predictive validity for indicators of programme functioning, supporting the appropriateness of this measure for identifying functional barriers to organisational change.^24–26^ This may be particularly relevant in the South African context since barriers to adoption of a new MNS service may not be specific barriers (eg, relating to the service itself), but rather general barriers related to the overall functioning of the facility. However, evidence in support of the TCU-ORC scale is HIC-specific and it is unclear whether the ORC items are relevant for LMIC contexts where resource allocation, leadership and other organisational dynamics within the public healthcare system are likely to be quite different from those in HIC settings. Although the TCU-ORC has been used in South Africa, with one study providing norms for this measure in the South African context,^27^ little is known about the measure’s psychometric properties in LMIC settings and South Africa specifically.^27^ Consequently, there is a need for contextually validating this measure. Further, the TCU-ORC in its current form is lengthy and time consuming to complete, comprising 125 items. Among measures used in implementation research, more than 60 items can be considered lengthy^23^ and may lead to reduced response rates. While it is important to ensure that measures provide a depth of information across a broad range of ORC constructs, this should be balanced with the administrative burden longer measures may present to health managers. Measures that are brief and represent low administrative burden may be more feasible and acceptable for management staff in low-resource settings who are often drawn into clinical work due to high patient burden.^28^ Developing a shortened version of the ORC may therefore enhance feasibility of assessing ORC within the context of South African PHC facilities.^29^ The process described in this study therefore aims to enable a reduction of items in the measure, while retaining the ability to collect the essential information required to inform effective implementation of a new service, thus aiming to balance quality and brevity.

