### Measures

This study will collect data from health managers and providers using three measures of ORC. All of these measures are self-report measures designed for use by healthcare staff and managers. The TCU-ORC scale is a comprehensive measure of ORC as it measures individual psychological factors and structural (health system) factors^30^ theoretically associated with ORC. It has four domains: Motivational Readiness for Change (33 items), Institutional Resources (31 items), Staff Attributes (31 items) and Organisational Climate (30 items).^24^ Each item is scored on a five-point Likert scale ranging from strongly disagree to strongly agree.

To assess convergent validity, two other measures with similar items will be used—the ORCA^31^ and the Checklist for Assessing Readiness for Implementation (CARI).^32^ The ORCA comprises three scales assessing (1) strength of evidence for the change to be introduced, (2) quality of the organisational context and (3) capacity for organisational facilitation of the change.^31^ There is some evidence for the overall reliability and factor structure of the ORCA; however, some of the subscales in the evidence scale have inadequate reliability and two of the ORCA subscales did not load significantly onto any of the three factor scales above.^31^ The CARI checklist includes assessment in eight key areas: organisational capacity, organisational climate or culture, staff capacity, system level capacity, functional considerations, senior leadership, training and implementation plan.^33^ This second instrument was selected because it contains items that are broadly similar in content and wording to the TCU-ORC items although data on its psychometric properties remain to be published. In addition, relevant demographic and work-related data, including age, gender, education level, profession and time in profession, will be collected from participants to examine differential response to items.

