### Participants and procedures

#### Aim 1: assessing internal consistency, construct validity and test-retest reliability of the TCU-ORC

Participants will be clinical staff from PHC facilities relevant to the implementation of Project MIND, as well as staff responsible for facility management and operations. These would include facility managers, operational managers, family physicians, medical officers, chronic care nurses, mental health nurses (where present), subdistrict managers (eg, PHC Managers), facility-based counsellors (employed by local non-governmental organisations) and their supervisors. We aim to secure participation of 12 appropriately selected staff members from each facility (288 participants from 24 facilities). Participants will be purposefully selected to complete the assessment, using the principle of maximum variation sampling to promote representation of the required health personnel cadres and management staff. If it is possible to recruit sufficient numbers for each staff category, we will explore areas of consensus or disagreement on the ORC measure by analysing the data by role. Preliminary meetings will be held with facility managers from each facility to identify the relevant personnel. At a ‘readiness workshop’ that will introduce facility staff to the Project MIND trial, written informed consent to participate in this organisational assessment process will be obtained. Consenting individuals will then be asked to provide some contact information to facilitate follow-up before self-completing the demographic questionnaire and three ORC questionnaires. They will be asked to complete the questionnaires after the workshop. One to 2 weeks after the workshop, participants will be asked to recomplete the questionnaires to enable test-retest reliability to be assessed. Participants will be offered a gift voucher to the value of R100 (~USD 10) to thank them for their time and participation.

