Although there has been little effort to investigate ORC in relation to chronic disease care and the integration of MNS services into chronic disease care in LMICs, there is evidently no ‘one size fits all’ solution for improving ORC in PHC facilities. The contextually validated ORC scale generated from this study will enable assessment of health facilities’ strengths and weaknesses in relation to adoption of any new health practices, beyond the specific focus of MNS services. Lower mean scores on the ORC domains will indicate potential areas of weakness; higher mean scores will indicate potential strengths.^46^ Understanding areas of good and poor performance will enable tailoring of implementation plans to address these strengths and weaknesses and consequently improve adoption and sustained implementation. Strategies to address barriers (eg, organisational culture barriers) may include providing information and effective participatory training on the new intervention, inclusive decision making with participation and discussion of all involved and addressing any concerns raised by front-line workers.^47^ An important critique of adoption of heath innovations in general, particularly in the Sub-Saharan African context, is that plans for sustainability of innovations are not put in place from the outset.^48^ Even in contexts where a new practice is readily adopted, ongoing effort is required to maintain delivery of innovative practices.^44^ Failing to understand PHC organisations’ ‘functional dynamics’^14^ and to support the process of organisational change through addressing barriers to change can reduce the likelihood of the change being sustained. A contextually appropriate ORCA tool may assist in identification of factors required to promote sustainability.

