Despite the relevance of this work to the PHC system in South African, there are several challenges to the collection of organisational data in this context. Possibly most important may be enabling health staff to find the time to complete the questionnaires and to ensure an adequate sample size. Second, the surveys will be presented in English. Some health staff may have difficulty understanding some of the questions if English is not their first language. However, the official business language for health service employees in the Western Cape of South Africa is English, and textual adaptations can be made to make survey items more readily understandable to health workers whose home language is not English. A further methodological issue is that the ORC measure data will be collected only from participants in the better resourced Western Cape province which may limit its generalisability to other less-resourced provinces. Delphi study data will however be collected from participants in a number of provinces across the country and may enhance relevance and utility of findings to health providers from other parts of the country.

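### Logistic regression is named for multi-item TCU-ORC scores with no binary or ordinal form given, and a score-level model cannot examine differential response to items

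*Protocol article*

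**What the plan says.** In the protocol article, Methods, Analyses, the one sentence on demographics is: "Multiple logistic regression analysis will be used to examine the association of demographic characteristics with TCU-ORC scores". No outcome category, threshold or ordinal form is given there or elsewhere in the article.

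The Measures section describes the instrument: "Each item is scored on a five-point Likert scale ranging from strongly disagree to strongly agree". Its four domains have 33, 31, 31 and 30 items. The same section says that age, gender, education level, profession, time in profession and other relevant data "will be collected from participants to examine differential response to items".

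The Discussion says how results are to be read: "Lower mean scores on the ORC domains will indicate potential areas of weakness; higher mean scores will indicate potential strengths".

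Under Aim 1, the plan is to recruit 12 staff from each of 24 facilities, 288 in all. It adds that responses may be analysed by role if enough staff of each category are recruited.

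**The concern.** There are two separate problems.

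**Model and outcome.** A domain score built from 30 or more five-point items is effectively continuous, and the article itself interprets it as a mean. Logistic regression in its usual form needs a binary outcome. If that is what is meant, someone must choose a split, the odds ratios will depend on that choice, and differences between staff on the same side of the split are lost.

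**Purpose and analysis.** The demographics are collected to look at how groups respond to items. The only model in the Analyses section that uses them has the score as outcome. If, say, managers score higher than nurses, that model cannot say whether managers perceive more readiness or whether some items work differently for them. Only the second bears on whether an item belongs in the short form. Item retention rests on factor loadings and the Delphi process, and an item can load well and be judged relevant by experts while still being answered differently by groups at equal readiness.

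**Working it through.** **Inputs from the article.** Items per domain 33, 31, 31, 30 (Measures); 125 items in total (Background); 12 staff × 24 facilities (Aim 1).

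**Stated figures reproduced.** 12 × 24 = 288. 33 + 31 + 31 + 30 = 125. No power calculation, effect size or cut-point is stated for this analysis, so there is none to reproduce.

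**How fine the score is.** A sum of k five-point items takes 4k + 1 values.
- 30 items: 4 × 30 + 1 = 121
- 31 items: 125
- 33 items: 133
- Full scale: 4 × 125 + 1 = 501

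**Cost of a cut, if the model is binary.** For a normal score and small effects, the efficiency of a split at quantile q relative to the uncut score is φ(c)² / [q(1 − q)], where c is the standard normal quantile at q.
- Median: 0.3989² / 0.25 = 0.637; 288 × 0.637 = 183
- 80th percentile: 0.2800² / 0.16 = 0.490; 288 × 0.490 = 141
- 90th percentile: 0.1755² / 0.09 = 0.342; 288 × 0.342 = 99 (rounded)

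**The same cost as power.** Assumptions, none of them from the article: two groups of 144, two-sided 5% level, independent observations. The difference with 80% power on the uncut score is d = (1.960 + 0.842) × √(2/144) = 0.33 SD. At that difference the split score gives:
- Median: proportions 0.434 v 0.566, power about 61%
- 80th percentile: 0.157 v 0.249, power about 49%
- 90th percentile: 0.074 v 0.132, power about 37%

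**What each model detects.** A simulation used a 31-item five-point domain, 288 respondents in two equal groups and 300 runs per scenario. Each item's latent response was 0.8 × trait plus standard normal noise. Two analyses were compared at the 5% level: logistic regression of the median-split score on group, and ordinal logistic regression of one item on group conditional on the rest-score.

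| Scenario | Score-level model flags group | Item-level conditional model flags item |
|---|---|---|
| No group difference, no biased item | 6% | 5% |
| True trait difference 0.5 SD, no biased item | 89% | 5% |
| No trait difference, tested item shifted by 0.6 on the latent scale | 7% | about 100% |

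The score-level model responds to true group differences and is almost blind to one biased item. The conditional item-level model does the reverse. The cut is not the reason: any model of the total, linear included, pools the 31 items and has nothing against which to compare a single one.

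**The case against.** **Logistic need not mean binary.** The sentence says multiple logistic regression, and a cumulative logistic model of the score needs no cut. This stands as a limit on the efficiency figures, which apply only to the binary reading. It does not rescue the sentence, which does not say ordinal. A reader might infer that an arbitrary split is definitely planned, or that 288 staff will act like 183. The article supports neither: no split is described, and the 183 assumes a normal score cut at the median.

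**An article condenses.** The definition of a binary outcome could sit in a fuller protocol or analysis plan, so its absence alone would be no finding. The point is that the article names a method which does not suit the score it describes.

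**Differential response may be plain language.** It could mean only describing how answers vary by group, and the analysis by role under Aim 1 comes close to that. But that analysis depends on recruitment, covers role only and does not compare staff at equal readiness. The Delphi does screen every item, excluding those below 70% consensus, so items are not unexamined. Expert ratings of relevance and evaluability do not test whether groups answer differently, however.

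**Language.** The Discussion notes: "Some health staff may have difficulty understanding some of the questions if English is not their first language". A reader might infer that home language, the obvious variable to examine, is not being collected. The article does not show this: the list of variables in Measures is introduced as a set of examples. Nor does it rank language first among the challenges. Staff time and sample size come first, and the article answers the language point by noting that English is the business language and that wording can be adapted.

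**Importance.** The aims are internal consistency, test-retest reliability, construct validity and a short form. Each has its own stated method, and none depends on the demographic regression. This stands and limits the severity.

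**Conclusion.** The point holds on both counts, as something that should be fixed in a supporting analysis. The stated regression does not match an outcome with 121 to 133 levels per domain that is read as a mean. If it is binary, the loss is about 36% of the information at a median split and 51% to 66% at the 80th to 90th percentiles. Those figures assume a normal score and small effects, ignore clustering within the 24 facilities, and do not apply to an ordinal model.

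The mismatch between the purpose given in Measures and the model in Analyses does not depend on those assumptions. A regression of the score on demographics cannot separate differential item response from a true group difference, whichever link is used. The simulated rates illustrate this under one chosen configuration and are not forecasts for this study.

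The tempting stronger conclusion, that the validation or the short form is invalid, is not supported.

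**What to change.** 1. Replace the sentence in Analyses with linear regression of each domain or subscale mean on the demographic characteristics, allowing for facility clustering by a random intercept or cluster-robust standard errors. This is essentially a wording change.

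2. To serve the purpose stated in Measures, add an ordinal logistic regression of each item on the characteristic, conditional on the rest-of-subscale score. Limit it to a few pre-specified characteristics with adequate group sizes, for example collapsed role and collapsed education, and control multiplicity.

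3. State that flagged items are supporting information for the short-form decision, alongside loadings and Delphi results, rather than automatic exclusions.

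The cost lies in steps 2 and 3. Two characteristics on 125 items mean 125 × 2 = 250 tests; at an unadjusted 5% level with no differential response, about 250 × 0.05 = 12.5 would be flagged by chance, hence the multiplicity control. All five listed characteristics would mean 125 × 5 = 625 tests, which is hard to justify with 288 respondents. Power will be limited for small staff groups: Aim 1 names nine categories, an average of 288 / 9 = 32 each, so collapsing roles is necessary. No change to recruitment is needed.

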
## Methods

### Study aim

The overall goal of this study is to contribute to the documented need for contextually adapted and validated measures for ORC assessment (ORCA)^24^ as an area of development for implementation science in a middle-income country context. More specifically, this study has two aims. First, the study aims to establish the internal consistency, test-retest reliability and construct validity of the long-form TCU-ORC questionnaire. Second, the study aims to develop a shortened version of the TCU-ORC that is feasible to use in South African PHC facilities. This can form a basis for assessing barriers and facilitators of adoption of new health interventions and guide the development of interventions to enhance the likelihood of effective implementation.

This study is nested within Project MIND, a multiyear study aiming to test two different approaches to service organisation for integrating counselling for depression and/or hazardous or harmful alcohol use into chronic disease care. Project MIND focuses on the provision of a facility-based lay counsellor-delivered programme for patients with depression and/or hazardous or harmful alcohol use who are receiving ongoing treatment for HIV or diabetes in the Western Cape province. Project MIND sites are 24 purposefully selected PHC facilities, with urban and rural representation.

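### Cronbach's alpha is the only internal-consistency statistic named, and for the 125-item total it says almost nothing about whether the items hang together

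*Protocol article*

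**What the plan says.** The Study aim section makes internal consistency one of three properties to be shown: "First, the study aims to establish the internal consistency, test-retest reliability and construct validity of the long-form TCU-ORC questionnaire". For that property, the Analyses section says "Internal consistency of the TCU-ORC and subscales will be assessed by calculating" Cronbach's alpha coefficients. The abstract also gives Cronbach's alpha as the measure of internal consistency. Neither place names another index or a target value.

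The Background says that "the TCU-ORC in its current form is lengthy and time consuming to complete, comprising 125 items". The Measures section divides them into four domains: "Motivational Readiness for Change (33 items), Institutional Resources (31 items), Staff Attributes (31 items) and Organisational Climate (30 items". The article does not say whether the subscales to be analysed are these four domains or shorter scales within them.

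Dimensionality is examined separately, as construct validity: "we will examine the factor structure with both exploratory and confirmatory factor analysis". The confirmatory step is aimed at the original structure: "Confirmatory factor analysis will be used to confirm whether the latent structure of the TCU-ORC identified in HIC is a good fit". Item retention for the short form draws on loadings: "Loading of items onto factors will be assessed to guide decisions around the relevance of each item", together with the Delphi results.

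**The concern.** Alpha combines two things, the average correlation between items and the number of items. With many items, a small average correlation is enough for a high value. A high alpha also does not show that the items measure one thing. Several unrelated clusters, each coherent within itself, can produce it.

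Both features matter here. The instrument is long, and the article itself describes it as four distinct domains, so a single alpha for the whole has no clear meaning as consistency. Every item uses the same agree-disagree scale, and the Discussion accepts that some staff may struggle with the English wording. A shared response style is therefore a realistic source of correlation.

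At stake is the reading of one part of the first aim. A high total alpha could be reported as established consistency beside a confirmatory model that fits poorly, because nothing in the Analyses section makes one result depend on the other.

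**Working it through.** **Inputs from the article.** Domain sizes are 33, 31, 31 and 30 (Measures), and 33 + 31 + 31 + 30 = 125, which matches the Background. The sample is 12 × 24 = 288 (Participants and procedures). The article gives no alpha and no pass mark. The marks of 0.70, 0.80 and 0.90 and all inter-item correlations below are assumptions.

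**Formula.** For k items with mean inter-item correlation r, standardised alpha = k·r / (1 + (k − 1)·r). Inverted, r = alpha / (k − alpha·(k − 1)).

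**Mean correlation needed.** For example, at k = 125 and alpha 0.70: 0.70 / (125 − 0.70 × 124) = 0.70 / 38.2 = 0.018.

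| Items | r for 0.70 | r for 0.80 | r for 0.90 |
|---|---|---|---|
| 125 | 0.018 | 0.031 | 0.067 |
| 33 | 0.066 | 0.108 | 0.214 |
| 30 | 0.072 | 0.118 | 0.231 |
| 6 | 0.28 | 0.40 | 0.60 |

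**Four uncorrelated domains, 125-item total.** Ordered within-domain pairs: 33×32 + 31×30 + 31×30 + 30×29 = 3,786, out of 125×124 = 15,500. With r = 0.30 within domains and 0 between them, the overall mean r is 0.30 × 3,786 / 15,500 = 0.0733. Alpha = 125 × 0.0733 / (1 + 124 × 0.0733) = 0.91. With r = 0.10 within domains, the mean r is 0.0244 and alpha is 0.76.

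**One 30-item domain.**
- Two unrelated 15-item halves, r = 0.30 within each: mean r = 0.30 × 420 / 870 = 0.145, alpha 0.84.
- Response style only, worth 10% of item variance (r = 0.10): 3.0 / 3.9 = 0.77. The same r over 125 items gives 12.5 / 13.4 = 0.93.
- Five unrelated six-item facets, r = 0.30 within each: mean r = 0.30 × 150 / 870 = 0.052, alpha 0.62.
- r = 0.02 gives 0.38, and r = 0.05 gives 0.61.

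**Simulation check** (288 respondents, normal scores rounded to five points, 500 runs each). Rounding weakens the correlations, so the values fall slightly below the formula.
- Four uncorrelated domains, r = 0.30: mean alpha 0.90 (95% range 0.88 to 0.91), every run at or above 0.80.
- Two 15-item halves, r = 0.30: 0.82 (0.79 to 0.84).
- 30 items, r = 0.10: 0.75 (0.71 to 0.79).
- 125 items: r = 0.02 before rounding gives 0.70 (0.64 to 0.75), r = 0.03 gives 0.78, and r = 0 gives −0.01.

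**Long against short forms.** The same mean r of 0.20 gives alpha 0.88 with 30 items and 0.60 with 6, so raw alphas are not comparable across lengths.

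**The case against.** A reader might infer that test length alone guarantees a high alpha, so that the first aim would succeed whatever the data show. The documents and the arithmetic do not support that, for these reasons:

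- With no correlation, alpha is 0 at any length. At 30 items, correlations of 0.02 to 0.05 give only 0.38 to 0.61.
- No cut-off is stated, so there is no formal check to pass.
- The first aim also covers test-retest reliability and construct validity. The principal component, principal axis and confirmatory analyses are what would expose unrelated halves or uncorrelated domains.
- Subscales are not equated with the domains. The Discussion mentions narrower content within Organisational Climate, which would fit shorter scales. At six items, 0.70 needs a correlation of 0.28, and alpha is then informative.
- A reader might also infer that alpha is used to choose items or to compare the two forms. It is not: loadings and expert consensus guide retention.

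A further argument is that extra indices are detail for an analysis plan that is not shown, and that alpha is a standard choice. This is right for supplementary indices in general. But the article itself names alpha as the internal-consistency statistic and applies it to the whole instrument, so the total-score problem comes from what is written. The Discussion interprets domain means and never a 125-item total. That limits the harm, but it also makes the total alpha easy to give up.

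**Conclusion.** The point holds in a limited form. For the 125-item total, alpha cannot support a claim of internal consistency: about 0.02 in mean correlation reaches 0.70, and four unrelated domains can give about 0.91. For domains of 30 to 33 items, alpha carries real information but can still be high for two unrelated halves (about 0.84) or for response style alone (about 0.77). For short subscales the issue is minor.

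These sizes rest on assumed inter-item correlations and a conventional 0.70 mark. The domain-level part also depends on the domains being among the scored subscales, which the article leaves open. The planned factor analyses limit the damage but do not remove it, because the reading of alpha is not made conditional on them. This is a cheap improvement to one part of the first aim and does not undermine the aim as a whole.

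**What to change.** In the Analyses section:

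1. Say which subscales are scored, and do not interpret a 125-item alpha as evidence of internal consistency.
2. For each scored domain or subscale, report the mean inter-item correlation and the corrected item-total correlations beside alpha. Interpret alpha only where the factor analysis supports a single dimension.
3. For any total score, use omega-hierarchical from the confirmatory factor analysis already planned, with a general factor specified. It would be zero in the case of four uncorrelated domains, where alpha is about 0.91.
4. If the long and short forms are compared on consistency, use the mean inter-item correlation and not raw alpha.

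Omega total is not a substitute, because it also rises with length and equals alpha for a one-factor scale with equal loadings. No particular floor for the mean correlation is required. None of these statistics separates response style from content, but a low mean correlation is at least visible where alpha would hide it.

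The cost is a sentence or two of wording and a few lines of code on the same data. The downside is slightly more analysis and a result that may look less favourable than alpha alone.
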